### Sample size

The study is powered to detect a significant difference in the primary outcome of death within the follow up period in the carer supported preferred location. Where the person with dementia has previously indicated a preferred location, this will be ascertained from and confirmed with the carer. Otherwise, the carer will be requested to nominate. Whilst there are large datasets that describe the location of death of people with advanced dementia, only two small studies from a recent systematic review provided data on preferred location of death [11].

Using this review to assume 60% of people with dementia in the control arm of the trial will die in a carer preferred location, then 408 participants will need to be enrolled in the study to have 90% power to detect a 15% increase in the proportion of people dying in preferred locations to 75%. The Type I error probability associated with these tests of this null hypothesis is 0.05. Applying a small (< 10% tolerance) to incomplete data and loss to follow up, we will enrol 440 participants, 220 per study arm.

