### Economic Evaluation Plan

A trial-based economic evaluation will take the perspective of the health care funder. Health care and intervention costs will be collected over the trial period. We will collect data on the cost to deliver the intervention (including staff costs, training, capital costs and consumables) as well as human and other resource costs associated with inpatient hospital admissions, ED presentations and other health service contacts. Inpatient admissions will be costed based upon Australian Refined Diagnosis Related Groups costs from the National Hospital Cost Data Collection; ED presentations will be costed using data from Independent Hospital Pricing Authority. All costs and savings will be adjusted to the base year using published deflators, and, if needed, costs incurred beyond one year will be discounted using a standard 5% discount rate.

Using mean costs and mean health outcomes in each trial arm, the incremental costs per 1) hospital death avoided; and 2) hospitalisation avoided compared with control group will be calculated; results will be plotted on a cost-effectiveness plane. Bootstrapping will be used to estimate a distribution around costs and health outcomes, and to calculate the confidence intervals around the incremental cost-effectiveness ratios. One-way and multi-way sensitivity analyses will be conducted around key variables and a probabilistic sensitivity analysis will estimate joint uncertainty in all parameters. A cost-effectiveness acceptability curve will be plotted to provide information about the probability that the intervention is cost-effective, given willingness to pay for each unit of benefit gained.

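### Bootstrap confidence intervals around the cost-effectiveness ratios cannot be interpreted if effect draws cross zero; an incremental net benefit interval from the same draws would avoid this.

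*Protocol article*

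**What the plan says.** The Economic Evaluation Plan compares mean costs and mean outcomes between arms: "the incremental costs per 1) hospital death avoided; and 2) hospitalisation avoided compared with control group will be calculated". Bootstrapping is then used to describe the distribution of costs and outcomes and "to calculate the confidence intervals around the incremental cost-effectiveness ratios". No condition is attached to that interval. The section does not name the type of bootstrap interval, gives no rule for draws with a zero or negative effect difference, and does not mention net benefit.

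Two other displays of the same uncertainty are planned. For the first, "results will be plotted on a cost-effectiveness plane". For the second, "A cost-effectiveness acceptability curve will be plotted to provide information about the probability that the intervention is cost-effective" at given values of willingness to pay. Deterministic and probabilistic sensitivity analyses are also listed.

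The Sample size section concerns a different outcome, death in the carer-preferred location: "408 participants will need to be enrolled in the study to have 90% power to detect a 15% increase" from a control rate of 60%, and "we will enrol 440 participants, 220 per study arm". Nothing comparable is given for hospital deaths or hospitalisations.

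**The concern.** A ratio of cost difference to effect difference behaves well only while the effect difference keeps one sign. As the effect approaches zero the ratio runs to plus or minus infinity, and it changes sign on the other side. A negative ratio may then describe an intervention that costs less and does more, or one that costs more and does less. A positive ratio may come from costs and effects that are both higher or both lower. Sorting such ratios and reading off the 2.5th and 97.5th percentiles pools draws with opposite meanings.

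The stake is how readable one planned output is. The Discussion of the article gives the economic results particular weight in arguing for investment in palliative care, so a funder should be able to read the interval that accompanies them. The problem would appear when the effect is most uncertain.

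**Working it through.** **1. The plan's own design figure.** Inputs from the Sample size section are 60% v 75%, power 90% and alpha 0.05 (taken as two-sided, which reproduces the figure). With the pooled formula,

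n per arm = [1.96 × √(2 × 0.675 × 0.325) + 1.2816 × √(0.60 × 0.40 + 0.75 × 0.25)]² / 0.15² = 202.8, so 203 per arm and 406 in total, against the stated 408. The figure reproduces.

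At 204 per arm the standard error (SE) is √(0.24/204 + 0.1875/204) = 0.0458, so 0.15/0.0458 = 3.28. The 95% interval would include zero in about 9% of trials, and only about 0.05% of bootstrap draws at the expected estimate would be at or below zero. This applies to the primary outcome with every participant contributing. Neither economic denominator is that outcome.

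**2. Hospital deaths per randomised participant.** The document gives no mortality and no hospital share of deaths, so both are assumed: 12-month mortality m of 40-60%, and a hospital share of 30-40% in the control arm, lower by 10-20 points under the intervention. There are 220 per arm and no losses. The rate in each arm is m × share, and SE = √[p₁(1 − p₁)/220 + p₂(1 − p₂)/220]. With D the true difference, the chance that the 95% interval spans zero is Φ(1.96 − D/SE) − Φ(−1.96 − D/SE).

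| Mortality | Hospital share | Rates | D (points) | SE (points) | Spans zero |
|---|---|---|---|---|---|
| 40% | 40% to 30% | 16.0% v 12.0% | 4.0 | 3.30 | 77% |
| 40% | 30% to 20% | 12.0% v 8.0% | 4.0 | 2.85 | 71% |
| 50% | 40% to 25% | 20.0% v 12.5% | 7.5 | 3.50 | 43% |
| 60% | 40% to 25% | 24.0% v 15.0% | 9.0 | 3.75 | 33% |
| 60% | 35% to 20% | 21.0% v 12.0% | 9.0 | 3.51 | 27% |
| 60% | 40% to 20% | 24.0% v 12.0% | 12.0 | 3.62 | 9% |

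The result depends almost entirely on the assumptions. Hospitalisations avoided could not be assessed, because the document gives neither a rate nor a variance for them.

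**3. What the ratio interval looks like when draws cross zero.** Take the first row (effect 4 points, SE 3.3). Assume a cost difference of 2,000 and a cost SD of 35,000, so that the SE of the cost difference is 35,000 × √(2/220) = 3,337. Costs and effects are drawn as independent normals.

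- About 11% of effect draws are at or below zero.
- The percentile limits of the ratio are about −660,000 and +800,000 per hospital death avoided.
- The quadrant shares are about 64% dearer and better, 24% cheaper and better, 8% dearer and worse, and 3% cheaper and worse.
- About a third of the ratios are negative. A quarter of those (8 out of 8 + 24) mean dearer and worse, and the rest mean cheaper and better.

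For contrast, take a 15-point effect with 204 per arm and an assumed cost difference of 1,000 (SE 1,500). The limits are about −15,000 and +35,500, with under 0.1% of draws at or below zero effect. The negative limit there plainly means a saving, and the interval is readable.

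**4. The same step-3 draws as net benefit.** Incremental net benefit is λD − C, where C is the cost difference and λ the willingness to pay. With λ = 100,000 per hospital death avoided (an assumed value, for illustration only), the estimate is 100,000 × 0.04 − 2,000 = 2,000. Its SE is √[(100,000 × 0.033)² + 3,337²] = 4,693, and the 95% interval is 2,000 ± 1.96 × 4,693, or about −7,200 to +11,200. It is finite and has one direction of benefit, whatever the sign of the effect draws.

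**5. Coverage.** In simulations with a cost SD of 35,000 and true differences of 2 to 7.5 points, percentile ratio intervals covered 96-99% and net-benefit intervals 95-96%, against a nominal 95%.

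**The case against.** Three arguments on the other side have force.

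First, the article does not say that percentiles of raw ratios will be used. Draws can be ordered by angle or quadrant on the plane, and a fuller economic plan may specify this. That is true, and the missing detail is no fault in itself. But the article commits to an interval around the ratio without condition. When the draws straddle zero effect, even an angle-ordered set passes through infinity and is not an ordinary range between two ratios.

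Second, the section already plans displays that cope with an effect spanning zero. The acceptability curve is the proportion of draws with positive net benefit at each willingness to pay, so the evaluation does not rest on the ratio interval alone. This stands and is the main reason that the point is minor. The curve gives a probability, however, not an interval estimate of the size of the benefit.

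Third, the coverage results in step 5 show mild over-coverage. This also stands: the defect is in interpretation.

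A reader might go further and infer that the effect will often span zero. The document gives no rates from which to say so, and the assumed settings run from 9% to 77%. The roughly 9% at the design effect does not settle it the other way, because it belongs to a different outcome. Nor does the document support calling the ratio interval meaningless in general, since it is sound while draws stay clear of zero effect. It also does not make that interval the main statement of economic uncertainty: it is one of several listed outputs, and the weight given in the Discussion is to the economic endpoints as a whole.

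**Conclusion.** The point holds in a limited and conditional form. The plan commits to confidence intervals around ratios whose denominators have no stated expected effect or power. If effect draws fall on both sides of zero, percentile limits of those ratios cannot be interpreted. The 9% to 77% range rests on assumed mortality and hospital shares, 220 per arm without losses, and a normal approximation. It shows that the situation is plausible, but not how likely it is. The consequence is an unreadable interval, not one shown to be too narrow. The plane and acceptability curve remain valid, and the primary analysis and sample size are untouched. It is worth correcting as a cheap improvement.

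**What to change.** In the Economic Evaluation Plan, name incremental net monetary benefit as the interval estimate. Report it for each outcome with its bootstrap 95% interval over a stated willingness-to-pay range, beside the planned plane and acceptability curve. Keep each ratio as a point estimate. If a ratio interval is shown at all, give the share of draws in each quadrant with it, so that the reader can see whether it is interpretable. A rule that shows the ratio interval only when the effect is statistically significant is best avoided, because reporting would then depend on the result.

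The cost is one extra summary from the same bootstrap samples and a change of wording. No data or trial conduct change. The one real burden is that a willingness-to-pay range must be chosen per hospital death avoided and per hospitalisation avoided. It should be fixed before results are seen.

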### Patient and Public Involvement

Authors IG and NC are consumer representatives with lived experience as carers of people that died of dementia and attended ED. They have contributed to the design of the recruitment strategy, intervention, the active control arm of the trial and the outcome measures.

## Discussion

There is very little high quality trial evidence to guide intervention in people dying of dementia. The most recent Cochrane review from 2016 found only one trial randomised at the individual participant level (*n* = 99) and concluded “that there is insufficient evidence to assess the effect of palliative care interventions in advanced dementia” [21]. A recent pilot RCT from the USA (*n* = 62) showed the feasibility and possible benefit of palliative intervention in this population [22].

Landmark research has shown that providing prognostic certainty amongst carers of people with advanced dementia substantially alters the rate of futile and invasive interventions before death [23]. Prior work shows ED attendance follows a predictable course in the last year of life, AND that course is highly modifiable through the use of palliative care [7].

This RCT will test an intervention co-designed by consumers with lived experience as carers of people who died of dementia, clinicians, and content specialists. It builds on prior trial learnings, notably a pilot of a trial led by some members of our team in Western Australia. CELPI will help carers make guided decisions to navigate the healthcare system to access specialist palliative care and other dementia services. CELPI will be delivered by a trained clinician and will incorporate education and coordination.

The intervention in this trial is focussed at the level of the carer. As noted in a recent position paper “proxy decision making can be confounded as such decisions may be impossible to separate from the family carers’ own views and furthermore, where the family carer has supportive (or other) care needs of their own” [24]. With this in mind, we have designed the CANDID measure to assess not only the needs of the person with dementia, but the needs of the carer, and will employ a suite of secondary outcome measures to assess carer strain and quality of life. The primary outcome of this trial (place of death) is commonly used in palliative care trials, however we recognise in many instances the person with dementia with capacity may not have had conversations with the carer, or provided written directives as to their preferred location of death.

A crucial feature in the design of this RCT is an active control arm, with all participants after randomisation receiving educational resources. While this study design element may risk contamination and dilution of the effect of the intervention, it was deemed crucial by our consumer investigators to provide all participants with the opportunity to seek help for a person who has been identified in the trial screening as approaching end of life with dementia. We believe the additional elements of the intervention are sufficient to trial whether this improves outcome over and above the passive provision of educational resources.

The research outcomes have potential to change current end of life practice and policies for older people dying of dementia and presenting to an ED. The findings from this project could positively impact on the design and implementation of end of life programs in Australia and internationally for people dying of dementia. A publication plan for the trial will be through peer review journals adjudicating the clinical and economic endpoints, with the latter particularly crucial for demonstrating the future benefits of investing in palliative care for people dying of dementia. Health policy changes arising from this trial will be advanced via the extensive clinical networks and health department links of the research team. We intend to launch any successful research report in conjunction with carer support organisations, advocating for policy changes to support carers.

## Data Availability

The datasets used and/or analysed during the current study are available from the corresponding author on reasonable request.

## Abbreviations

ED: Emergency Department
CELPI: Carer End of Life Planning Intervention
RCT: Randomised Controlled Trial
MMSE: Mini Mental State Examination
MoCA: Montreal Cognitive Assessment
FAST: Functional Assessment Staging Test
AKPS: Australia-modified Karnofsky Performance Status
QUALID: QUAlity of Life in late stage Dementia
SAS: Symptom Assessment Scale
MCSI: Modified Carer Strain Index
MBRI: Modified Bereavement Risk Index
RGS: Research Governance Service
ACTRN: Australian Clinical Trials Registration Number
